### Withdrawal or dropout criteria

Patients will not be included in the analysis if:The researchers find out after randomization that the participants were included by error or misdiagnosis.Participants were not administered the research medication as planned because:They received the research medication for > 24 h;They failed to receive the research medication;They received the research medication for < 5 days (not including the patients who were discharged due to improved health or death due to progression of the illness);The actual dosage was < 80% of the total dosage (compliance < 80%).The major data were missing, affecting the evaluation of the efficiency of the main indicators.Prohibited medication was used or the combined medication dosage exceeded that of the protocol, thereby affecting the evaluation of the efficiency.Due to complications or changes in the condition, other specific treatment measures were accepted that were not suitable for continuation in this study.Voluntary withdrawal.

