### Intervention

#### Trial treatment methods

After randomization, the participants will be categorized into two groups receiving either XBJ injection (specification, 10 mL/piece; packaging, 10 pieces/container) or placebo (0.9% NaCl injection, suggested specification, 200 mL). XBJ injection is provided and manufactured by Tianjin Chase Sun Pharmaceutical Co., Ltd., Tianjin, China (lot number Z20040033). The 0.9% NaCl injection is provided by each sub-center. Both groups will receive routine medication according to the GOLD 2016 guideline [17].

The treatment group will receive routine medication plus XBJ injection every 12 h (q12h) for 60 min; a total of 50 mL XBJ will be diluted to 150 mL using 100 mL of 0.9% NaCl injection. The control (placebo) group will receive routine medication plus 0.9% NaCl injection (dosage 150 mL, q12h for 60 min). The dosage and speed of injection for the placebo and XBJ injection groups (150 mL, q12h, intravenous drip for 60 min) will be identical. The patients will receive the research medication within 24 h of enrollment, and the treatment period is 5 days.

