#### Precautions

The following precautions will be observed:The use of other injections simultaneously during the course of intravenous infusions is prohibited.Other injections should be separated into 50 mL 0.9% NaCl.Prohibited medicines include ulinastatin, and TCM injections, such as Tanreqing, Reduning, and Qingkailing with efficacy similar to that of XBJ.The routine treatment of AECOPD should be carried out simultaneously, and XBJ injection should not be used as a substitute.If medication is administered for < 5 consecutive days and the patients’ clinical symptoms improve significantly resulting in discharge or the condition deteriorates, necessitating other treatments, the administration of the research medication will be suspended. The data for the first day of withdrawal will be recorded to day 6, and the follow up will be continued until day 28.

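### The 80% dosage exclusion does not carry the exemption of the item before it; measured against the full 5-day course, it removes exempt early stoppers with 7 or fewer of 10 infusions

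*Protocol article*

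**What the plan says.** All of this is in the protocol article.

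- **Withdrawal or dropout criteria.** The list opens with "Patients will not be included in the analysis if" and names no analysis set. Among the reasons for medication not having been given as planned are two adjacent items on exposure. One excludes patients with fewer than 5 days of medication, "not including the patients who were discharged due to improved health or death due to progression of the illness". The next excludes a patient if "The actual dosage was < 80% of the total dosage (compliance < 80"%). The second item has no exemption, and the total is not defined.
- **Trial treatment methods.** Each infusion is "150 mL, q12h, intravenous drip for 60 min" in both arms, and "the treatment period is 5 days". For the active arm, "a total of 50 mL XBJ will be diluted to 150 mL using 100 mL of 0.9% NaCl injection".
- **Precautions.** If a patient improves and is discharged before 5 consecutive days, or deteriorates and needs other treatment, "the administration of the research medication will be suspended". It continues: "The data for the first day of withdrawal will be recorded to day 6, and the follow up will be continued until day 28".
- **Statistical analysis.** The main analysis uses the FAS, which requires at least one treatment and sets no compliance threshold. The primary outcome is tested in the FAS. The PPS is limited to patients who completed without protocol violation or deviation. Both sets are used for efficacy.

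**The concern.** Each item in the list excludes on its own, so being spared by one gives no protection from the next. The exemption shows that the authors did not want to lose patients whose treatment was short because they went home better or died of their illness. If the 80% is taken of the full course, the following item loses many of those same patients.

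The patients removed are defined by events after randomization: quick recovery or early death. These overlap the trial's own outcomes, since 28-day mortality and length of hospitalization are secondary endpoints. An early death after intubation would also drop out of the intubation count. A treatment that changes the speed of recovery or early mortality would change who is removed from each arm, so the remaining groups would no longer be comparable by randomization. The loss is also avoidable, because Precautions keeps early-discharged patients in follow-up to day 28.

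**Working it through.** The plan gives no figure for the total dosage or for the number of patients affected, so there is none to reproduce on this point. The sample size of 127 per group, raised to 150 for attrition (127 / 0.85 = 149.4), reproduces and is not in question.

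**Inputs** (Trial treatment methods): one infusion every 12 hours, 5 days, 50 mL XBJ per infusion; threshold 80% (Withdrawal or dropout criteria).

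**Total under the full-course reading**
- Infusions: 2 per day × 5 days = 10.
- XBJ: 10 × 50 mL = 500 mL. Control volume: 10 × 150 mL = 1,500 mL.
- Threshold: 0.80 × 10 = 8 infusions (400 mL XBJ), the same count in both arms. Exactly 80% is not below 80%, so 8 whole infusions pass.

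**A patient discharged improved or dead from progression, with every infusion given until then**

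| Infusions given | XBJ (mL) | Given / 10 | Fewer-than-5-days item | 80% item, full course | 80% item, dose scheduled to the stop |
|---|---|---|---|---|---|
| 4 (2 full days) | 200 | 40% | kept (exempt) | removed | kept (100%) |
| 6 (3 full days) | 300 | 60% | kept (exempt) | removed | kept (100%) |
| 7 | 350 | 70% | kept (exempt) | removed | kept (100%) |
| 8 (4 full days) | 400 | 80% | kept (exempt) | kept | kept (100%) |
| 9 | 450 | 90% | kept (exempt) | kept | kept (100%) |

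The two items disagree for 1 to 7 infusions and agree for 8 and 9. The disagreement depends entirely on the denominator. If the total is the dose scheduled up to discharge or death, a fully dosed early stopper scores 100% and no such patient is removed.

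**Direction of bias.** Take an arm of n patients with e intubations.
- Removing m early discharges who were never intubated changes the rate from e/n to e/(n − m), which is higher.
- Removing d early deaths after intubation changes it to (e − d)/(n − d), which is lower whenever some of the remaining patients were not intubated.

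The net effect on the between-arm difference depends on m and d in each arm, so it can go either way.

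**Number affected.** The article gives no distribution of early discharge or death. Each 1% of the 300 patients is 3 patients; the percentage itself is unknown.

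**The case against.** **The full-course denominator is an inference.** This stands. A reader might take it as stated that compliance is measured against the 5-day dose, but the article never says so. It is still the natural reading. The item sits under medication not given as planned, and no other total can be derived from the text.

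**A patient whose drug was suspended under Precautions was treated as planned, so neither item applies.** This is arguable. However, the fewer-than-5-days item sits under the same heading and still needed an explicit exemption, so the heading alone cannot be relied on to protect these patients.

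**Compliance derivations belong in the statistical analysis plan.** This stands as far as it goes: a missing definition alone would not be a finding. The point here is that two exclusion rules are written out next to each other, and on the only derivable total they treat the same patient in opposite ways.

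**The primary analysis is protected.** This stands if Statistical analysis governs. A reader might infer that the primary intubation comparison loses these patients, but the FAS as defined there keeps everyone treated at least once. The inference holds only if the unqualified wording that opens the exclusion list takes precedence.

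**Two further inferences fail.** A reader might see a second contradiction in a non-exempt patient who stops after 4 full days, passes the 80% item and fails the 5-day item. Those are simply two alternative grounds for exclusion, and failing one is enough. Nor does the 80% item remove all early improvers and early deaths, since those with 8 or 9 infusions are kept.

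**Conclusion.** The concern holds in a limited form. The exemption is attached to one exposure item and not to the next, whose denominator is undefined. If that denominator is the planned course, the 80% item reverses the exemption for patients with 1 to 7 of 10 infusions and leaves it intact for those with 8 or 9.

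The consequence is outcome-dependent selection in the per-protocol efficacy comparison, with unpredictable direction and a size that the article does not allow one to estimate. The conclusion rests on the full-course reading and on counting whole infusions. It extends to the primary analysis only if the Withdrawal or dropout criteria override the FAS definition; those two sections conflict as written and must be reconciled. The sample size is unaffected. This should be corrected, but it does not undermine the main analysis if the FAS governs.

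**What to change.** 1. For the 80% item, define compliance as infusions given divided by infusions scheduled up to the earliest of day 5, improved discharge or death from progression. The exemption then holds in both items. The fewer-than-5-days item can stay as a separate ground.
2. State that the exposure exclusions in the Withdrawal or dropout criteria define the PPS only and do not remove anyone from the FAS.
3. Word the PPS definition so that a stop covered by the exemption is not counted as a deviation.

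This changes analysis-set wording and leaves treatment as it is. It needs one derived variable, from infusion counts and the date and reason of stopping. The existing 80% item already presupposes dosing data, and the Follow up section has data recorded daily during the intervention; the full data-capture schedule is in a figure not available here. The downside is small: the PPS will include some patients with short exposure. The change applies the plan's own exemption consistently and goes no further, so patients stopped early for deterioration without death would still be excluded by the fewer-than-5-days item, and the PPS would remain a supportive set.

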### Sample size

A previous study [27] by the Collaborative Research Group of Noninvasive Mechanical Ventilation for COPD showed that the tracheal intubation rate in the routine treatment group (171 cases) was 15.2%, while it was 4.7% in the group receiving early noninvasive positive pressure ventilation plus routine treatment (171 cases). According to the literature, presuming that the rate of tracheal intubation in the XBJ group was reduced from 15.2% to 4.7%, the sample size was calculated according to the parameters α = 0.05 (two-sided test) and β = 0.2. Comparing the rates of the two groups with respect to the sample size estimation formula, we calculated that 127 patients should be recruited in each group. Considering an attrition rate of < 15%, the eligible participants in each group should be > 149. Therefore, we determined that the sample size should be 150 in each group (*n* = 300 in total).

### Randomization

We will use an independent interactive web response system (IWRS) and adopt the method of competition to enter into the group to complete the randomization. The number of participants in the XBJ and control groups is nearly in the ratio of 1:1.

When a sub-center accepts an eligible participant, the investigators will enter the baseline information (including the subject’s screening number, abbreviated name, age, gender, medical history) in the central randomization system. Then, the central randomization system will assign an identification code (SSID, 6 digits) and a random number (4 digits), which is unique for each participant.

The drug administrators will log into the central randomization system after the random number is generated, and assign the research medication to the nurses according to the group information based on the random number.

### Blinding

The blinding method is consistent with our previous study [28]. Briefly, both investigators and subjects will be blinded, while drug administrators and dispensing nurses are aware of the group allocation. But the drug administrators and dispensing nurses will not be involved in data collection and analysis. In order to mask the investigators, drug administrators and the investigators would have independent authority to log into the central randomization system. The subjects’ group allocation is concealed by the randomization system, and both the paper and electronic case report form (CRF) collect only the patient’s random number, which does not indicate the group allocation. The evaluators and statistician will also be masked until completion of the visit and analysis. Both XBJ and placebo are administered using a photophobic infusion set to avoid the subjects being aware of the group information.

#### Emergency unblinding

The patient’s group allocation should be known in the event of an emergency and can be obtained from the drug administrators. Researchers should contact the principal within 24 h to report the reasons for unblinding. The precise cause of unblinding, the date of the emergency, the treatment situation, and the results must be reported in the CRF. After unblinding, the case will be withdrawn and the data will be recorded to day 6 of the trial evaluation.

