**Methods:**

This study will be a prospective, randomized, placebo-controlled, blinded, multi-center trial. A total of 300 eligible patients will be randomly assigned to the treatment or placebo control group in a 1:1 ratio using a central randomization system. The treatment group will receive routine medication plus XBJ injection, and the control group will receive routine medication plus 0.9% NaCl injection. The patients will receive the corresponding treatment for 5 days starting within 24 h of enrollment. The primary outcome, the of rate endotracheal intubation, will be evaluated on day 28 after treatment. The secondary outcomes will include changes in immune and inflammatory indicators, respiratory support, mortality rate after 28 days, blood gas analysis, improvement in Acute physiology and chronic health evaluation (APACHE) II scores and clinical symptoms, and the length and cost of intensive care unit stay and hospitalization. The safety of the interventions will be assessed throughout the trial.

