#### Secondary outcome measures

The secondary outcome measures will be:Changes in immune indicators (detected by flow cytometry).Changes in inflammation indicators (detected by enzyme-linked immunosorbent assay).Respiratory support: the duration of oxygen therapy, high-flow humidification oxygen therapy, noninvasive mechanical ventilation, and invasive mechanical ventilation.Mortality rate after 28 days.Blood gas analysis (including blood lactate).Improvement in acute physiology and chronic health evaluation II (APACHE II) scores; the evaluation of improvement is based on differences in the APACHE II scores before and after the intervention.Improvement in clinical symptoms based on improvement in dyspnea, cough, sputum, and the use of accessory respiratory muscles (using the scoring system shown in Table 2). According to the differences in the scores before and after the intervention, the evaluation criteria are as follows:Significantly effective: the score decreased ≥ 3;Effective: the score decreased from 1 to 3;Ineffective: no change in the score;Exacerbation: the score increased ≥ 1;Name, dosage, and duration of antibiotic use.Name, dosage, and duration of corticosteroid use.Changes in laboratory inspection indicators.Incidence of complications.Length and cost of intensive care unit (ICU) stay.Length and cost of hospitalization.

**Table 2 Tab2:** The clinical symptoms scoring system of AECOPD

Score	Dyspnea	Cough	Sputum production	Use of accessory respiratory muscles
0	–	No cough	No sputum	No neck muscle tension and periodic contraction
1	Shortness of breath when flat on the ground or walking up one floor level	Intermittent cough, but no symptoms at night	Sputum volume ≤ 30 mL the whole day and night	Neck muscle tension, but no obvious muscle activity
2	Shortness of breath when walking with peers	Sometimes cough, which probably affects sleep	Sputum volume ≥ 30 mL and ≤ 50 mL	Visible slight contraction of the neck muscles
3	Need to stop so as to breathe when walking at their own speed	Frequent cough affecting sleep	Sputum volume ≥ 50 mL and ≤ 100 mL	Moderate contraction of the neck muscles, not with clavicular fossa and intercostal retraction
4	Shortness of breath when dressing or undressing	–	Sputum volume ≥ 100 mL	Strong contraction of the neck muscles, with abdominal contradictory movement

The evaluation criteria for the improvement in clinical symptoms is according to the total scores of the 4 items

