### Follow up

Various parameters are followed up according to the data collection time points (Fig. 2).Screening period (1 day): 24 h before recruitment.Intervention period (5 days): follow up and recording of data every dayPeriod after intervention (within 28 days after treatment): follow up on days 6 and 28. If the patient is discharged, contact is established via telephone or a short messaging service.

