### Statistical analysis

An independent professional statistician and researcher will develop a complete statistical analysis plan for the trial, prior to the final analysis. The statistical analysis will be performed by the statistician in a blinded manner using the Statistical Analysis System (SAS) software version 9.2. The main analysis will be based on the full analysis set (FAS). According to the intention-to-treat principle, the FAS refers to a set of data on any participants who randomly receive at least one treatment. The per-protocol set (PPS), a subset of the FAS, includes data on only those participants who completed the trial without any violations of or deviations from the protocol. The FAS and PPS will be used for the assessment of efficacy. For the safety assessment, the safety set (SS) will be used, which includes patients who have received at least one safety evaluation after treatment.

All data, including the number of subjects included, drop-outs, elimination conditions, demographics, baseline characteristics, and efficacy and safety assessment, will be analyzed using different approaches. Descriptive and univariate statistics will be used to characterize the study participants and compare the baseline characteristics between the two groups. The primary outcome is the rate of endotracheal intubation, which will be determined by the Cochran-Mantel-Haenszel (CMH) test in the FAS population. We prefer to use the CMH chi-square test because it can deal with confounders of multi-center effects. Two-sided tests will be performed for all the other statistical analyses. The CMH chi-squared test or Fisher’s exact test will be used for comparing the categorical outcomes. The continuous outcomes will be analyzed by Student’s *t* test, while the AEs will be presented using descriptive statistics and compared using a chi-square test. A *P* value <0.05 will be considered to indicate statistical significance. Missing data will be explored and adjusted using the imputation method.

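### Emergency-unblinded patients are withdrawn with data to day 6 and no stated day-28 follow-up, although the primary outcome and mortality are day-28 outcomes

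*Protocol article*

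**What the plan says.** All references are to the protocol article.

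- **Emergency unblinding.** The trigger is that the patient's "group allocation should be known in the event of an emergency". The consequence is: "After unblinding, the case will be withdrawn and the data will be recorded to day 6 of the trial evaluation". Nothing is said about day 28.
- **Precautions.** Patients who stop study drug before five days, either because they improve and are discharged or because they deteriorate and need other treatment, come under a fuller rule: "The data for the first day of withdrawal will be recorded to day 6, and the follow up will be continued until day 28".
- **Outcomes.** The Abstract says that the primary outcome, intubation, "will be evaluated on day 28 after treatment". The secondary outcomes include "Mortality rate after 28 days". After the intervention period, the Follow up section schedules "follow up on days 6 and 28", with telephone or text-message contact for discharged patients.
- **Statistical analysis.** The main analysis follows the intention-to-treat principle, and "the FAS refers to a set of data on any participants who randomly receive at least one treatment". Missing data are to be imputed by a method that is not named.

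**The concern.** The two rules treat similar patients differently. Someone who deteriorates and stops study drug is followed to day 28. If the code is also broken, the rule that names this situation withdraws the patient, records data to day 6 and stops there. Breaking the code does not prevent anyone from observing a later intubation or death, so the rule itself would create the missing data.

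Two things are at stake. First, the missingness is unlikely to be unrelated to outcome, because an emergency prompts the unblinding. Second, a treated patient belongs to the FAS by definition but would lack the endpoint that the FAS is meant to compare. If unblinding were more frequent in one arm, the comparison could shift. The trial expects few events, so a small number of lost ones is not negligible.

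**Working it through.** **1. The plan's own figure.** Inputs from Sample size: intubation 15.2% against 4.7%, two-sided α = 0.05, β = 0.2. The pooled-variance formula for two proportions is

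n = [1.96·√(2·p̄·(1−p̄)) + 0.842·√(p₁(1−p₁) + p₂(1−p₂))]² / (p₁−p₂)², with p̄ = (0.152 + 0.047)/2 = 0.0995.

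It gives 127 per arm, as stated. Allowing for 15% attrition, 127/0.85 = 149.4, so 150 per arm. The sample size is not at fault. With all 150 per arm observed to day 28, power is 86.3%.

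**2. Expected events.** 150 × 0.152 = 22.8 and 150 × 0.047 = 7.05, together 29.85, or about 30 intubations. The average planned risk is 29.85/300 = 9.95%.

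**3. Events at risk.** The article gives no unblinding frequency. Assume 2%, that is 0.02 × 300 = 6 patients.

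| Assumed risk of a first intubation after day 6 among the six | Events lost | Share of 29.85 |
|---|---|---|
| Average planned risk, 9.95% | 6 × 0.0995 = 0.6 | 2% |
| 50% | 3 | 10% |
| 100% (ceiling) | 6 | 20% |

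The first row is not a floor. It places the whole planned risk after day 6, whereas some intubations would occur earlier and be recorded.

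**4. Effect on power if events are lost in equal proportion in both arms (150 per arm).**

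| Events lost | Power, lost events counted as non-events | Power, those patients excluded |
|---|---|---|
| 0% | 86.3% | 86.3% |
| 10% | 82.1% | 82.8% |
| 20% | 76.9% | 78.5% |
| 30% | 70.8% | 73.3% |

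Power stays above the planned 80% at a 10% loss and falls below it at 20%.

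**5. Effect if only one arm loses events.** Take no true effect, with 15.2% in both arms. If three event patients in one arm are excluded, its rate becomes (22.8 − 3)/147 = 13.5%, a spurious difference of 1.7 percentage points. One lost patient gives 0.6 points and five give 2.9. If three lost events are instead counted as non-events, the shift is 3/150 = 2.0 points. The planned difference is 15.2 − 4.7 = 10.5 points.

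**The case against.** The best reply is that the text is ambiguous rather than wrong. Precautions uses nearly the same day-6 phrase and couples it with day-28 follow-up. The phrase may therefore mean only that the data are entered as the day-6 evaluation. Emergency unblinding does not forbid later follow-up, and a patient who deteriorates and stops drug early arguably falls under the Precautions rule whether or not the code was broken. This stands in part: a reader might infer an express order to collect nothing beyond day 6, and the article does not say that. Even so, the rule written for this situation withdraws the case and omits the day-28 clause that its counterpart contains. A site following it would have no instruction to make the day-28 contact.

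Three stronger readings are tempting and not supported:

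- **That the sickest patients as a group lose the outcome.** Deterioration and intubation are not stated triggers for unblinding, and deteriorating patients who stop drug are followed to day 28. Treatment lasts five days, so an intubation during an emergency on treatment would largely be captured by day 6.
- **That safety is understated.** The safety section says that subjects with adverse events are followed, and the safety set needs only one safety evaluation after treatment.
- **That 20% of events would be lost.** This is a ceiling. It needs both the assumed 2% unblinding rate and a first intubation after day 6 in every one of the six.

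FAS membership is also already defined. What is lacking is the outcome, not the definition. The unnamed imputation method may be left to the analysis plan and is no defect in itself, but no method turns an uncollected outcome into an observed one.

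**Conclusion.** The point holds in this limited form. The unblinding rule is out of step with the early-stopping rule, with the day-28 outcomes and with the intention-to-treat analysis. Followed as written, it leaves intubations and deaths after day 6 uncollected in unblinded patients, for a reason plausibly linked to prognosis.

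The size cannot be derived from the article. At an assumed 2% unblinding rate it runs from about 0.6 events (2%) at the average planned risk to a ceiling of 6 (20%). At the low end the effect on the trial is slight. At the ceiling, with proportionate loss in both arms, power falls just below 80%. The link to prognosis is an inference from the emergency trigger, and any difference between arms in unblinding is hypothetical. The case for acting rests on how easily the loss can be avoided, not on a demonstrated large bias.

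**What to change.** Reconcile Emergency unblinding with Precautions and Statistical analysis. Suggested wording: *After emergency unblinding the patient remains in follow-up. Intubation and death are recorded to day 28, by telephone or text message if the patient has been discharged. The patient is analysed in the FAS in the assigned arm; unblinding affects per-protocol membership only.*

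The article should also say that a case withdrawn under this rule is not thereby removed from the main analysis. The section on withdrawal or dropout criteria opens by excluding the patients it lists. Unblinding is not on that list, but the shared term invites the confusion.

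The change concerns data collection and analysis only and leaves treatment decisions after unblinding untouched. The sample size stays at 150 per arm. The cost is a short amendment, the ethics re-review that the article requires for protocol changes, and one day-28 contact per unblinded patient by a route the Follow up section already provides. Recruitment is reported as ongoing, so it should be made promptly: day-28 outcomes not collected at the time may be hard to recover.
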